## Method/design

### Objective

The objective of this study is to compare the efficacy of DS treatment combined with acupuncture with that of placebo combined with acupuncture for pain reduction in patients with acute lateral ankle sprain (ALAS) in order to investigate the efficacy of DS for the treatment of ankle sprain.

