### Hypothesis

Our null hypothesis is that the pain control effects of DS are not superior to those of placebo in patients with ALAS.

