#### Primary outcome

Because the objective of this study is to investigate the efficacy of DS therapy for pain relief in patients with ALAS, changes in the pain severity (measured using VAS) will be considered as the primary outcome. The VAS will be a 10-cm straight line marked at each end with the anchor labels “no pain” and “pain as bad as it could be” [35]. Patients will be asked to mark the line at a point representing their severity of pain. Scores will be recorded in millimeters, with a total score range of 0–100 mm [36].

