### Statistical analysis

Baseline characteristics will be compared between the two groups. Repeated measures analysis of covariance (RM ANCOVA) will be performed to determine differences between groups, considering the different baseline characteristics (covariance). Continuous data will be presented as means and standard deviations and compared using the independent *t* test or Wilcoxon’s rank sum test, while categorical data will be presented as frequencies and percentages and compared using the chi-square or Fisher’s exact test. VAS scores for pain and the secondary outcomes (FAOS, edema, and EQ-5D-5 L scores) will be evaluated by RM ANCOVA. Dependent variables will include values measured before, at the end of, and at 4 weeks after treatment completion. Changes in the VAS score from baseline to treatment completion (visit 5) and 4 weeks after treatment completion (visit 6) will be determined by the paired *t* test. A repeated contrast test will be performed to account for time differences in each group. A *P* value of < 0.05 will be considered statistically significant. We will perform per-protocol analysis for the assessment of efficacy and a supplementary full analysis set. All statistical analyses will be performed using SPSS version 22.0 (SPSS Inc., Chicago, IL, USA).

Data for subjects who meet the dropout criteria (*i.e.*, < 80% compliance with the protocol, incidence of SAEs, reluctance to continue the trial, incomplete data that could influence the trial, large error in protocol or significant deviation in implementation, and decision to terminate trial participation by the PI or IRB) will be excluded. Missing values will be implemented by multiple imputations. In addition, differences between subjects who complete the study and dropouts will be statistically analyzed to determine whether any particular factor is significantly associated with participation dropout. Interim analyses will not be performed.

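### RM ANCOVA is named for the between-group comparison of VAS, but no visit or model term is fixed as the test of DS versus placebo, and change in VAS is assigned to paired t tests that do not compare the arms

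*Protocol article*

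**What the plan says.** The Objective is comparative: to "compare the efficacy of DS treatment combined with acupuncture with that of placebo combined with acupuncture for pain reduction". The Hypothesis section follows it: "Our null hypothesis is that the pain control effects of DS are not superior to those of placebo in patients with ALAS". Neither names a visit or an effect measure.

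Under Primary outcome, "changes in the pain severity (measured using VAS) will be considered as the primary outcome", again with no visit. Table 1 schedules VAS at visit 1 (before treatment), visit 5 (end of treatment) and visit 6 (4 weeks later).

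The Statistical analysis section contains three strands for VAS:

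- **Between-group model.** "Repeated measures analysis of covariance (RM ANCOVA) will be performed to determine differences between groups", and "VAS scores for pain and the secondary outcomes (FAOS, edema, and EQ-5D-5 L scores) will be evaluated by RM ANCOVA". The dependent variables are the values at all three time points, the pre-treatment one included. Covariates are described only as differing baseline characteristics; baseline VAS is not named.
- **Change in VAS.** The method given is a paired t test: "Changes in the VAS score from baseline to treatment completion (visit 5) and 4 weeks after treatment completion (visit 6) will be determined" in that way.
- **Time contrasts.** "A repeated contrast test will be performed to account for time differences in each group".

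One threshold, P<0.05, covers everything. Sidedness, an order of testing and a multiplicity rule are not stated. Sample size estimation gives 24 per group as a pilot, with no power calculation.

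**The concern.** The primary outcome is defined as a change, and the one sentence that analyses VAS as a change, with its visits, names a test that leaves allocation out. A paired t test asks whether pain moved from baseline. In acute sprain, with acupuncture given to both arms, pain may well fall without any contribution from DS. A significant paired result is therefore no evidence for DS, and neither is a significant result in one arm beside a non-significant result in the other.

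The RM ANCOVA is the right kind of analysis, but as written it can yield a group main effect, a group-by-time interaction or a contrast at either post-treatment visit. None is tied to the null hypothesis. At stake are an error rate that depends on which result is later called primary, and lost power if the term chosen averages in a time point at which DS cannot yet have acted.

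**Working it through.** **Inputs from the protocol.** 24 per arm; VAS at baseline, visit 5 and visit 6; P<0.05. The plan gives no SD, correlation, effect size or power, so there is no figure of its own to reproduce.

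**Assumptions.** Unit SD at each visit, equal correlation ρ between visits (0.3, 0.5, 0.7), two-sided tests, all 24 per arm analysed. Simulations used 20,000 trials per setting, with improvement at visit 6 set to 1.2 times that at visit 5.

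**1. Paired tests when DS has no effect.** Both arms improve by 0.5 SD at visit 5. The SD of change is √(2(1−ρ)), and the chance p of significance in one arm is the paired-t power at n = 24 for 0.5/√(2(1−ρ)). The arms are independent, so the chance of a significant DS arm and a non-significant placebo arm is p(1−p).

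| ρ | SD of change | standardized change | p | p(1−p) | simulated |
|---|---|---|---|---|---|
| 0.3 | 1.183 | 0.423 | 0.51 | 0.25 | 0.252 |
| 0.5 | 1.000 | 0.500 | 0.65 | 0.23 | 0.234 |
| 0.7 | 0.775 | 0.645 | 0.86 | 0.12 | 0.121 |

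Counting either visit, the simulated figures are 0.371, 0.320 and 0.149. With a common improvement of 1.0 SD, both arms are almost always significant and the split at visit 5 falls to 0.023 or less.

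In millimetres, a paired test with n = 24 has power 0.96 for a 20 mm fall with SD of change 25 mm and 0.9999 for 30 mm with SD 25. It has 0.76 for 20 mm with SD 35, 0.47 for 10 mm with SD 25 and 0.35 for 10 mm with SD 30.

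**2. Several between-group results, each at 0.05, under the null.** The bound for k independent tests is 1 − 0.95^k.

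| What may count as success | independence bound | simulated two-sided error |
|---|---|---|
| one pre-specified contrast | 0.05 | 0.048-0.052 |
| change at visit 5 or visit 6 | 1 − 0.95² = 0.0975 | 0.089-0.093 |
| either visit, or the group main effect | 1 − 0.95³ = 0.1426 | 0.134-0.140 |

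**3. The choice of term.** Take ρ = 0.5 and a true effect δ at both post-treatment visits, zero at baseline.

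- *Group main effect over three levels, baseline VAS not a covariate.* The effect on the mean is 2δ/3 and its SD is √((1+2ρ)/3) = √(2/3) = 0.816. For δ = 0.5: 0.333/0.816 = 0.408, power 0.28.
- *One visit, adjusted for baseline VAS.* Residual SD is √(1−ρ²) = √0.75 = 0.866. For δ = 0.5: 0.5/0.866 = 0.577, power 0.50.
- *Mean of both post-treatment visits, adjusted for baseline VAS.* Residual SD is √((1+ρ)/2 − ρ²) = √0.5 = 0.707. For δ = 0.5: 0.5/0.707 = 0.707, power 0.67.

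For δ = 0.8 the three powers are 0.60, 0.88 and 0.97.

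The first figure depends on baseline VAS being left out of the covariates. If it were a covariate as well as a repeated level, the baseline part of the mean would be fixed by the covariate. The standardized effect would then be (2δ/3)/((2/3)×0.707) = δ/0.707, as in the third case. The text does not say which applies.

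**4. Precision.** The unadjusted 95% half-width for a difference at one visit is t(0.975, 46) × √(2/24) = 0.581 SD.

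**The case against.** The strongest reply is that the plan does state a between-group analysis. RM ANCOVA is specified to find group differences and is applied to VAS by name. That stands: a reader might infer that none of the stated tests addresses DS versus placebo, and the text contradicts this.

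A reader might also infer that a within-arm result could be declared a success. No section sets such a rule, and a paired test cannot reject the stated null. That the paired tests are run separately by arm is likewise an inference, because the plan speaks of each group only for the repeated contrasts. Pooling the arms would not help, since allocation would still play no part.

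It is fair, too, that the paired tests need not be significant: there is no minimum VAS at entry, and the milder settings above give power of 0.35 to 0.76. The visit-specific contrasts behind the 9% and 14% are possible readings, not tests listed in the plan. Those rates also count results favouring placebo. In the DS direction alone, simulation gives about 4.4-4.5% for two contrasts and 6.8-7.0% with the main effect added, against 0.05/2 = 2.5% for one contrast. The 0.581 SD half-width assumes no exclusions, whereas efficacy is analysed per protocol.

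Finally, an analysis plan that is not shown may settle the visit and the term, and this is a declared pilot. Both lower the severity. Neither removes the point: the published text already assigns the primary change to a paired test and lists baseline as an outcome level, and it keeps a superiority null with a significance threshold.

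**Conclusion.** The point holds in limited form, at moderate severity. The method that the plan attaches to change in VAS does not compare the arms. The model that does compare them has no designated visit or term and treats the pre-treatment value as an outcome.

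The sizes rest on assumed SDs, correlations and improvements, because the protocol gives none. With no DS effect and 0.5 SD improvement in both arms, a misleading split at visit 5 arises in about 12-25% of trials if paired tests are run by arm; it is far rarer if improvement is large. Leaving the visit open gives about 9% two-sided error, and leaving the main effect open as well gives about 14%. A main effect that includes the baseline level, without baseline VAS as a covariate, has about 0.28 power for a 0.5 SD effect at correlation 0.5, against about 0.50 for a baseline-adjusted contrast at one visit.

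**What to change.** Name one primary analysis: the between-group difference in VAS at one pre-specified visit, for example visit 5 at the end of treatment, adjusted for baseline VAS and reported as an estimate with a two-sided 95% CI. The documents do not rank visit 5 above visit 6, so the choice is the sponsor's, but it must be fixed before unblinding.

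Use baseline VAS as a covariate and take it out of the repeated outcome levels. Make the other visit secondary. Keep paired and within-group changes as description, without significance tests. As this is a pilot, state that the conclusion rests on the estimate and its interval, and that P≥0.05 is not evidence of no effect.

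The cost is a change of analysis wording; no new data are needed. The one loss is that the visit not chosen can no longer carry the primary claim.

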### Study design

The present study design is in accordance with the Standard Protocol Items: Recommendations for Interventional Trials (SPIRIT) and Consolidated Standards Of Reporting Trials (CONSORT) 2010 guidelines [31, 32] (see Additional file 1). The study is a randomized, double-blinded, placebo-controlled, parallel-arm, single-center (Semyung University Korean Medicine Hospital in Chungju, Republic of Korea) clinical trial with a 1:1 allocation ratio. A total of 48 participants who meet the inclusion and exclusion criteria will be randomly allocated to a DS (*n* = 24) or a placebo (*n* = 24) group. Patients in both groups will receive acupuncture treatment once a day for 5 days a week (excluding Saturday and Sunday) and the trial medication (DS/placebo capsule) three times a day for seven consecutive days. The primary outcome measure will be pain relief evaluated using a Visual Analog Scale (VAS). The secondary outcome measures will be Foot and Ankle Outcome Scores (FAOS), edema, European Quality of Life Five-Dimension-Five-Level Scale (EQ-5D-5 L) scores, and the number of recurrent ankle sprains. VAS, FAOS, edema, and EQ-5D-5 L scores will be assessed before, at the end of, and at 4 weeks after treatment completion. EQ-5D-5 L scores will be additionally recorded at 26 weeks after treatment completion. The number of recurrent ankle sprains will be recorded at 4, 8, 12, and 26 weeks after treatment completion.

This study protocol complies with the principles of the Declaration of Helsinki and Korean Good Clinical Practice guidelines and has been approved by the Ministry of Food and Drug Safety (registration number, 20160318110). The trial has been registered at cris.nih.go.kr (registration number, KCT 0002374). The study design is summarized in Table 1 and Fig. 1.

**Table 1 Tab1:** Treatment schedule and outcome measures

	Study period										
	Enrollment	Allocation	Post allocation								Close-out
Timepoint	Screening		Visit1	Visit2	Visit3	Visit4	Visit5	Visit6	Visit7	Visit8	Visit9
	Week		1					5	8	13	27
Enrollment											
Informed consent	X										
Sociodemographic profile	X										
Medical history	X										
Vital signs	X	X	X	X	X	X	X	X			
Inclusion/exclusion criteria	X										
Allocation		X									
Clinical laboratory tests	X						X				
Interventions											
Acupuncture treatment			X	X	X	X	X				
Trial medication prescription			X								
Assessments											
Change of medical history			X	X	X	X	X	X	X	X	X

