### Intervention

Both groups will receive acupuncture treatment once a day for 5 days a week (excluding Saturday and Sunday) and the trial medication (DS/placebo capsule) three times a day for seven consecutive days. Treatment will be administered by Korean medicine physicians with 6 years of formal university training in Korean medicine, a licence to administer treatment, and at least 1 year of clinical experience. To ensure strict adherence to the study protocol, the physicians will receive training together and employ the same techniques.

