#### Acupuncture treatment

All participants will receive acupuncture at the ST36, ST41, BL60, BL62, KI3, KI6, GB39, and GB40 points on the affected side [25]. Only sterile, stainless steel, disposable acupuncture needles (size, 0.25 × 30 mm; Dong Bang Acupuncture, Inc., Boryeong, Republic of Korea; product no. A84010.02) with guide tubes will be used. The depth of insertion will be 10–20 mm depending on the location of the needle [34]. After insertion, the needles will be left in position for 15 min in every session. Manual stimulation and electroacupuncture will not be applied (see Table 2).

**Table 2 Tab2:** Revised STandards for Reporting Intervention in Clinical Trials of Acupuncture (STRICTA)

	Item criteria	Description
1.Acupuncture rationale	1a. Style of acupuncture	Korean Medicine Therapy
	1b. Reasoning for treatment provided – based on historical context, literature sources, and/or consensus methods, with references where appropriate	1. Discussion among four physicians who practice Korean medicine (consensus) 2. Textbook of acupuncture and moxibustion medicine 3. Relevant articles [20] Selection of treatment regions based on textbooks, related papers, and expert discussions
	1c. Extent to which treatment varied	Standardized treatment
2. Details of needling	2a. Number of needle insertions per subject per session (mean and range where relevant)	8
	2b. Names (or location if no standard name) of points used (uni-/bilateral)	ST36, ST41, BL60, BL62, KI3, KI6, GB39, GB40
	2c. Depth of insertion, based on a specified unit of measurement or on a particular tissue level	The depth of insertion is 10 to 20 mm, depending on the location of the needle [21]
	2d. Responses sought	No *de qi* or muscle twitching – only sensation due to needle insertion
	2e. Needle stimulation	None
	2f. Needle retention time	15 min per session
	2 g. Needle type	sterile, stainless, disposable acupuncture needles (size 0.25 × 30mm; Dong Bang Acupuncture, Inc., Boryeong, Republic of Korea; product no: A 84010.02)
3. Treatment regimen	3a. Number of treatment sessions	5
	3b. Frequency and duration of treatment sessions	Five times/week for 1 week, 15 min per session
4. Other treatment components	4a. Details of other interventions administered to the acupuncture group	None

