#### Trial medication

The trial medications will include DS and placebo capsules, which will be identical in appearance, taste, and smell. The DS formulation composed of granular extracts of nine herbal substances, will be a gray-brown powder contained in a 0.6-g pink capsule (Fig. 2). The placebo will be composed of 300 mg of corn starch, 150 mg of lactose hydrate, 1.5 mg of magnesium stearate, and 48.5 mg of caramel colorant. Both medications will be administered at a dose of three capsules three times daily (total daily dose, nine capsules) for a period of 1 week.

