### Outcome measurements

VAS, FAOS, edema, and EQ-5D-5 L scores will be assessed before, at the end of, and at 4 weeks after treatment completion. EQ-5D-5 L scores will be additionally recorded at 26 weeks after treatment completion. The number of recurrent ankle sprains will be recorded at 4, 8, 12, and 26 weeks after treatment completion.

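### Visit 5 is called treatment completion, but it falls on medication day 5 of 7 for Monday starters; separately, Table 1 puts Visit 7 one week earlier than the text implies

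*Protocol article*

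**What the plan says.** The Intervention section sets two schedules that run side by side. For acupuncture: "Both groups will receive acupuncture treatment once a day for 5 days a week (excluding Saturday and Sunday". The STRICTA table in the Acupuncture treatment section gives five sessions in all: "Five times/week for 1 week, 15 min per session". For capsules: "the trial medication (DS/placebo capsule) three times a day for seven consecutive days". The Trial medication section gives the amount as "three capsules three times daily (total daily dose, nine capsules) for a period of 1 week".

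Table 1 in the Study design section, titled "Treatment schedule and outcome measures", places the acupuncture sessions at Visits 1 to 5, all in week 1, and the prescription of trial medication at Visit 1. It marks VAS, FAOS, edema and EQ-5D-5L at Visits 1, 5 and 6, and laboratory tests at screening and Visit 5. The Outcome measurements section describes the middle one of the three VAS readings as the end of treatment, and the Statistical analysis section attaches that label to a visit: "Changes in the VAS score from baseline to treatment completion (visit 5".

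For later follow-up, the Outcome measurements section states: "The number of recurrent ankle sprains will be recorded at 4, 8, 12, and 26 weeks after treatment completion". Table 1 dates the four corresponding visits, 6 to 9, in weeks 5, 8, 13 and 27.

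**The concern.** The acupuncture course pauses for the weekend and the capsule course does not. The fifth session therefore need not coincide with the last medication day, yet the plan treats Visit 5 as the end of treatment for everyone. VAS change is the primary outcome and Visit 5 is its first post-baseline reading. If that reading comes at different points of the capsule course depending on the weekday of enrollment, the end-of-treatment comparison does not have one meaning. The same holds for the other measures taken at Visit 5. The later visits, which are counted from treatment completion, inherit the unclear starting point.

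The Visit 7 week is a separate and smaller matter. Table and text give different dates for one recurrence count, so staff who follow the table and staff who follow the text would schedule it a week apart.

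**Working it through.** The document gives no calculation to reproduce here. The check is a calendar count.

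**Visit 5 against the capsule course**

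Inputs from the document: one session per weekday and none at weekends (Intervention); five sessions at Visits 1 to 5 (STRICTA table, Table 1); medication prescribed at Visit 1 (Table 1) and taken for seven consecutive days (Intervention).

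Assumptions: sessions fall on consecutive weekdays with no holiday or missed visit, and the first dose is taken on the day of Visit 1. The document does not state the day of the first dose.

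Counting the day of Visit 1 as day 1:

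| Start day | Session days | Visit 5 on day | Medication days left after it |
|---|---|---|---|
| Monday | 1, 2, 3, 4, 5 | 5 | 7 − 5 = 2 |
| Tuesday | 1, 2, 3, 4, 7 | 7 | 0 |
| Wednesday | 1, 2, 3, 6, 7 | 7 | 0 |
| Thursday | 1, 2, 5, 6, 7 | 7 | 0 |
| Friday | 1, 4, 5, 6, 7 | 7 | 0 |

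The interval from the baseline VAS at Visit 1 to Visit 5 is 5 − 1 = 4 days for Monday starters and 7 − 1 = 6 days for the rest.

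If the first dose is instead taken the day after Visit 1, Visit 5 falls on medication day 5 − 1 = 4 for Monday starters and 7 − 1 = 6 for the others. The two-day gap between the groups remains, and nobody has finished the course at Visit 5.

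**Table 1 weeks against the text**

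The treatment occupies week 1, so x weeks after completion is week 1 + x.

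| Visit | Weeks after completion (text) | 1 + x | Table 1 | Agrees |
|---|---|---|---|---|
| 6 | 4 | 5 | 5 | yes |
| 7 | 8 | 9 | 8 | no |
| 8 | 12 | 13 | 13 | yes |
| 9 | 26 | 27 | 27 | yes |

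The other possible rule, table week = x, gives 4, 8, 12 and 26 and agrees only at Visit 7. No single rule produces all four printed weeks.

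**The case against.** **Size.** For four of the five possible start days, Visit 5 is the last medication day, and the share of Monday starters is unknown. Patients may enroll at any time within 72 h of injury, so time since injury already varies by up to three days, more than the two days at issue. The repeated-measures analysis also uses Visit 6, when the capsule course is over for everyone. The trial is a declared pilot with no sample-size calculation, so no stated power is lost. All of this stands, and it limits the weight of the point. It does not remove the contradiction: the enrollment window does not change how much of the course has been taken at Visit 5, or how long after baseline the reading comes.

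**Condensed article.** Visit windows are commonly left to the full protocol. That is fair for windows, but here the article itself equates a visit with the end of treatment, and its own schedule contradicts this.

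**Stronger readings that the document does not support**

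- *A biased comparison.* The timing rules are identical in two randomized, blinded arms. Start days could be unevenly split by chance with 24 per arm, but that is noise and not systematic bias.
- *A calculable dilution of the effect.* This would need the share of Monday starters and the shape in which an effect builds up over the week. The document gives neither.
- *Fully adherent Monday starters failing the 80% compliance rule.* By the end of day 5 at most 9 × 5 = 45 of 9 × 7 = 63 capsules (71%) can have been taken. But the document gives no date for returning the boxes and does not define compliance as capsules taken out of 63 at Visit 5. Measured against capsules due by then, the figure is 45/45 = 100%.
- *No safety follow-up after the last dose.* Safety assessment and vital signs continue at Visit 6. Only the laboratory tests come before the end of the course for Monday starters.
- *A fault in a key outcome at Visit 7.* That visit carries only the secondary recurrence count and the update of medical history.

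**Conclusion.** The point holds in a limited form. Under the stated assumptions, the plan's schedule does not deliver the end-of-treatment time point to Monday starters: their VAS, FAOS, edema, EQ-5D-5L and laboratory tests at Visit 5 come two medication days early. If dosing begins the day after Visit 1, the label fits nobody. The consequence is a mislabelled time point that mixes two exposure lengths and adds noise to the first post-baseline reading of the primary outcome. Its effect on the estimate cannot be quantified from the document.

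The Visit 7 conflict is certain from the printed figures and needs no assumption beyond the one-week treatment period. It amounts to one week, affects a secondary outcome, and is minor. Both are worth correcting because the correction is cheap.

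**What to change.** Reconcile the Intervention, Outcome measurements and Statistical analysis sections with Table 1, leaving both treatment schedules as they are. The sponsor should state what treatment completion means and on which day dosing starts, then choose one of two routes for the end-of-treatment reading:

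1. Take the end-of-treatment VAS on one fixed elapsed day from first dose for every participant, collected the same way for all. The VAS is marked by the patient, so a dated form completed by everyone would serve. Giving the form only to Monday starters would make the mode of collection depend on start day. The cost is self-completed forms outside the clinic and a way to get them back, since no visit is scheduled between Visit 5 and Visit 6.
2. Keep the reading at Visit 5, define it as the time of the fifth acupuncture session, and stop calling it treatment completion. This costs only wording, but leaves the two exposure lengths mixed.

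Under either route, label the timing of the edema measurement and laboratory tests for what it is, and do the same for FAOS and EQ-5D-5L if they stay at Visit 5. State the day from which the follow-up weeks are counted. Finally, make the Visit 7 week agree, by correcting either the table or the text; this is a one-figure change.

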**Fig. 2 Fig2:**
[figure not shown]
Appearance of *Dangguixu-san* (DS) and placebo capsules used in the study

The manufacturing process for the DS capsules is as follows. First, 0.63 g of *Angelicae gigantics radix*, 0.42 g of *Paeoniae radix rubra*, 0.42 g of *Linderae radix*, 0.42 g of *Cyperi rhizoma*, 0.42 g of *Sappan lignum*, 0.33 g of *Carthami flos*, 0.29 g of *Persicae semen*, 0.25 g of *Cinnamomum cassia*, and 0.21 g of *Glycyrrhizae radix* are added to the extractor. The mixture is extracted with 8–10 volumes of purified water at 80–100 °C for 3–4 h. The extract is filtered (100 mesh), concentrated under reduced pressure at ≤ 60 °C, and dried to obtain 350 mg of a granular extract. Then, 45 mg of lactose hydrate, 100 mg of corn starch, and 5 mg of magnesium stearate are mixed into the granular extract, and the mixture is converted into granules, dried, crushed, and filled into capsules.

Capsules will be sourced from Kyungjin Pharmaceutical Co., Ltd. (Icheon, Gyeonggi-do, Republic of Korea (product no. 02190)). The medication will be dispensed as 0.6-g capsules packed in sealed boxes containing a 1-week dose.

Between the preintervention period and 4 weeks after treatment completion, participants will not be allowed to take the following drugs: NSAIDS, pain relievers, steroids, or adherent inflammatory pain relievers; drugs containing potassium, licorice, glycyrrhizic acid, furosemide, ethacrynic acid, or trichloromethazine; and drugs containing any of the main ingredients of DS. Participants will be asked to return their medication boxes to allow enumeration of leftover capsules and for monitoring participant adherence.

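### Efficacy in a superiority comparison rests on the per-protocol set, and the exclusion rule is not confined to that set, so post-randomisation exclusions can bias the VAS result in either direction

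*Protocol article*

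**What the plan says.** The Hypothesis section of the protocol article sets up a superiority comparison: "Our null hypothesis is that the pain control effects of DS are not superior to those of placebo in patients with ALAS". Under Primary outcome, "changes in the pain severity (measured using VAS) will be considered as the primary outcome".

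The Statistical analysis section then fixes the analysis sets: "We will perform per-protocol analysis for the assessment of efficacy and a supplementary full analysis set". Its second paragraph lists the dropout criteria under which a subject's data are left out: "< 80% compliance with the protocol, incidence of SAEs, reluctance to continue the trial, incomplete data that could influence the trial", and further "large error in protocol or significant deviation in implementation, and decision to terminate trial participation by the PI or IRB) will be excluded". The sentence does not say which analysis set it governs. The next one reads "Missing values will be implemented by multiple imputations". The same section sets a significance threshold of P < 0.05.

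Nowhere does the article make the full analysis set primary or co-primary, or say which set prevails if the two disagree.

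**The concern.** Every listed criterion is an event after randomisation. Several can depend on how much pain a participant has or how well the capsules are tolerated: reluctance to continue, compliance below 80%, an SAE. Once such participants are removed, the groups compared are no longer those that randomisation created. If removal is related to pain and more frequent in one arm, that arm keeps its milder cases and looks better on the VAS. This can produce an apparent DS effect where there is none, or hide a real one.

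There is also a structural problem. Because the exclusion sentence is not tied to the per-protocol set, it can be read as applying to the full analysis set too. Excluding subjects for incomplete data also conflicts with imputing missing values, since those are largely the subjects for whom imputation is needed. The supplementary analysis may therefore not offer the protection that its name suggests.

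**Working it through.** **Step 1: the text.** The analysis set for efficacy is stated explicitly, so this is not a detail left to a fuller document. Set beside the superiority hypothesis, the order of the two sets is reversed. The exclusion criteria are all post-randomisation and carry no restriction to one set.

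**Step 2: is there a figure to reproduce?** No. Under Sample size estimation, 24 per group was set by feasibility, with no effect size, SD, power or dropout rate. What follows is illustration only.

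**Step 3: bias and type I error.**

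Input from the document: 24 per arm, and significance at 0.05 (taken as two-sided, since sidedness is not stated).

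Assumed: SD 20 mm, no true difference, normal outcome, two-sample t test. The probability of exclusion follows a logistic model, logit(p) = a + ln(4.5) × u, where u is a standardised score and a is set to give the stated exclusion rate in each arm. In model A, u is the analysed VAS score itself. In model B, u is a variable correlated 0.5 with that score. There were 20,000 replicates per scenario. Bias is in favour of the arm with more exclusions.

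| Excluded, arm 1 / arm 2 | Model A: bias, type I error | Model B: bias, type I error |
|---|---|---|
| 15% / 15% | about 0 mm, 0.049 | about 0 mm, 0.049 |
| 25% / 25% | about 0 mm, 0.050 | about 0 mm, 0.048 |
| 5% / 10% | 1.2 mm, 0.054 | 0.6 mm, 0.052 |
| 5% / 15% | 2.3 mm, 0.067 | 1.1 mm, 0.054 |
| 5% / 25% | 4.3 mm, 0.109 | 2.1 mm, 0.063 |

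In participants, 5% of 24 is 1.2, 15% is 3.6 and 25% is 6, so the last row means about one exclusion against six.

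**Step 4: a different exclusion model.** Here all exclusions come from participants with worse-than-median pain (20,000 replicates, SD units). Excluding 10% / 10% gave about 0 bias and type I error 0.053; 20% / 10% gave 0.11 SD and 0.067; 20% / 0% gave 0.20 SD and 0.098. At the assumed 20 mm, 0.11 × 20 = 2.2 mm and 0.20 × 20 = 4 mm, which is the same order as model A. Reversing the imbalance reversed the sign.

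**Step 5: the alternative.** Under the step 4 model, analysing all randomised participants with complete outcomes gave bias of about 0 and type I error of 0.047 to 0.051 in every scenario.

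**Step 6: precision.** The 95% CI half-width is t × 20 × √(2/n). For n = 24, 2.013 × 20 × √(2/24) = 11.6 mm. For n = 19 (about 20% excluded), 2.028 × 20 × √(2/19) = 13.2 mm. This loss is secondary to the bias.

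**The case against.** The best defence is that this is a single-centre pilot sized by resources, described in the Discussion as giving preliminary evidence. It is double-blind with identical capsules, which limits arm-dependent decisions about whom to exclude. Treatment lasts one week. A full analysis set result is promised, and a comparison of completers with dropouts is planned. All of this lowers the likely size of the problem. It does not remove it: a test at P < 0.05 is still planned, blinding does not stop tolerability or lack of relief from differing by arm, and the VAS is also analysed 4 weeks after treatment. The completer comparison is not stated to be by arm, and the full analysis set may be cut by the same exclusion sentence.

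The defence also rightly limits what can be claimed. Three stronger readings are tempting and unsupported:

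- **That prohibited analgesic use and gastrointestinal complaints are exclusion routes.** Under Trial medication, "Between the preintervention period and 4 weeks after treatment completion, participants will not be allowed to take the following drugs", a list that covers NSAIDs and pain relievers. The section on adverse events mentions nausea and diarrhoea. But the dropout criteria name neither analgesic use nor ordinary AEs. They count only if they are treated as a significant deviation, cause low compliance or lead to reluctance to continue. That the participants in most pain would deviate most often is plausible but not documented.
- **That the result would be tilted towards DS.** Nothing shows which arm would lose more. If pain drives exclusion and placebo is less effective, placebo loses more and the bias goes against DS.
- **That the false-positive rate doubles.** That needs a five-fold imbalance in exclusions driven directly by the analysed score. With equal exclusions there was no inflation.

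**Conclusion.** The point stands. The plan names the wrong leading set for a superiority comparison, and its exclusion sentence is loose enough to affect both sets. The conclusion rests on the text and does not depend on the simulation.

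The size cannot be known from the document. With SD 20 mm, 24 per arm and no true effect, all assumed apart from the sample size, the bias runs from about zero with equal exclusions, through about 1–2 mm with type I error of 5–7% at 5% versus 15%, to about 2–4 mm and 6–11% at 5% versus 25%. Where in each range it falls depends on how strongly exclusion tracks the VAS score. The direction is open.

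The full analysis set is free of this bias when outcomes are complete. Where they are missing, it depends on the imputation model being adequate.

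**What to change.** In the Statistical analysis section:

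1. Make the full analysis set primary for efficacy, defined as all randomised participants, analysed as allocated, regardless of compliance or deviations, with multiple imputation for missing values.
2. Confine the exclusion sentence to the per-protocol set, so that incomplete data lead to imputation, not removal, in the primary analysis. Swapping the labels of the two sets without this step could leave the same participants out.
3. Keep the per-protocol analysis as a sensitivity analysis.
4. Decide per-protocol exclusions before unblinding and report them by arm and reason.

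The cost is a rewrite of the analysis-set sentence and the exclusion paragraph, with no change to the 24 per group. The downside is a possibly smaller estimated effect where non-compliance dilutes it.
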